## Methods

### Summary

We present the methods section in parts. We first present a detailed description of the data we plan to use as our source including the architecture of the databases and data elements. Program data are currently held in different databases located in Gurugram and call data records are held in the Mobile Network Operator’s datacenter in Delhi. Next, we provide a description of the data munging (ie, data wrangling) and analysis methods including a brief description of the various machine algorithms under consideration.

### Data Sources and Flow

Auxiliary nurse midwives collect and register details of pregnant women and, after delivery, of postpartum women and children born in their catchment areas. These data are captured in print registers and uploaded at the block level by data entry operators, forming the data in the pregnancy tracking databases. The data collected include personal identifiers such as geographic location, names of women and a mandatory mobile phone number, and where available, details of the pregnancy and childbirth. Data capture happens at two key time points: (1) the earliest is the registration of the woman at the time of the identification of pregnancy, and (2) following childbirth, when the details for delivery care are available. In actual practice, these events may happen many days or months after the event (pregnancy registration or birth of child) has happened.

Figure 1 summarizes the databases and flow of data for both Mobile Academy and Kilkari. The following are existing databases:

State-based databases that pre-date existing Mother-Child Tracking System (MCTS) and are integrated with MCTSMCTS database at the national levelReproductive Child Health (RCH) database at the national levelCall data records captured by Mobile Network Operator stored separately in their databases and used mainly for billing purposesCall data records of Kilkari subscribers and ASHAs’ usage of Mobile Academy captured by the IVR system and stored in the IVR database in a data center contracted by the governmentMobile Technology for Community Health (MOTECH) database, which is integrated with the RCH and MCTS databases and integrates information from call data records with a small set of MCTS and RCH data for each userManagement Information System database, which extracts data from MOTECH and generates reports. The sampling frame for both Mobile Academy and Kilkari are derived from the MCTS and RCH data. Data from the RCH and MCTS databases are pulled into the MOTECH database on a predetermined schedule every day.

**Figure 1 figure1:**
[figure not shown]
Summary of data flow for Kilkari and Mobile Academy.

### Ethical Considerations

The registration data on pregnant women and ASHAs are collected by the Ministry of Health and Family Welfare of the Government of India and the ministries of health of the states participating in the program. The data will be analyzed under a data sharing agreement with the Bill & Melinda Gates Foundation and Johns Hopkins University, University of Cape Town, and BBC Media Action. The Institutional Review Boards of Johns Hopkins School of Public Health, Sigma in New Delhi, India, and the University of Cape Town have provided the ethical certification for the study.

### Data Processing

For the Kilkari program, the pregnant women or postpartum women’s data are captured in the RCH and MCTS systems, or in state-based systems that then pass data to RCH or MCTS, and from there to the MOTECH system. Before the data are accepted by MOTECH, the system automatically runs validations to check that the mobile numbers are in the correct format, locations match location masters in the MOTECH database, and last menstrual period and date of birth are within the Kilkari timeframe. The MOTECH system uses the last menstrual period or the delivery date to determine the schedule of messages to be delivered. The MOTECH engine provides the list of phone numbers (clients) to be called each day to the IVR system, which then calls the numbers and plays the appropriate pre-recorded message, which is stored in the IVR system’s content management system. If the call is not answered, then the IVR system attempts to call again at least 3 times every day for 4 days until the call is answered.

For the Mobile Academy program, details on ASHAs including their names, phone numbers, geographic location, and age are contained in either the RCH or MCT databases, or in state-based databases integrated with MCTS and used to register them to Mobile Academy. The MOTECH engine captures these data on ASHAs from the RCH or MCTS databases and following registration to Mobile Academy, ASHAs are eligible to call in to the IVR system using the same phone number provided in the RCH database. The IVR system validates the phone number against the MOTECH system and then retrieves the “bookmark” information that details the status of the ASHA and her progress on the list of content expected to be covered. Based on this information, the appropriate content is delivered to the ASHA via the IVR system and the updated data return to the MOTECH database.

### Analysis

The data from the databases (Figure 1) will be extracted onto secure password-protected hard drives from each server storage. Merging data files will be complex given the nature of identifiers across databases. An MCTS record does not have a beneficiary ID. Instead, it has a “Mother” (pregnancy) ID or a “Child” ID. In other words, MCTS tracks pregnancies and births, rather than women. When Kilkari first went live in October 2015, it mirrored the MCTS approach and generated subscription IDs for each pregnancy and then birth. However, the new RCH database does have a unique beneficiary ID, which enables the system to track an individual woman through her multiple pregnancies and the births of children. The architecture of the MOTECH database and Kilkari was changed in December 2016 to introduce a unique beneficiary ID and MOTECH was then integrated with RCH in mid-2017. There is an additional complexity, namely that MOTECH used to allow multiple Kilkari subscriptions on one mobile number, assuming a single phone could be shared by a number of women in a joint family. However, a decision was made to remove this feature in 2017 (July 28 for RCH and October 6 for MCTS) due to the complexity it created in analyzing system-generated data. Hence the analytic time horizon assumed in the analysis may span from 2017-2018 after the MCTS-RCH integration occurred and the aforementioned changes were made. The merging of datasets will occur in India, and only de-identified data will be stored on the hard drives and used in this analysis. As part of Study Aim 1, we will examine the quality of the data for completeness, including patterns and any geographic clustering in missingness.

### Additional Data From Baseline Surveys of Evaluation of Kilkari and Mobile Academy

Analyses described in this section are being carried out as part of a larger external evaluation of Kilkari. We describe concurrent efforts to undertake a randomized controlled trial (RCT) in the state of Madhya Pradesh (MP) for Kilkari, inclusive of baseline surveys with pregnant and postpartum women, and ASHA workers. Once identified as part of baseline survey activities and randomized to receive Kilkari content (or no content at all), phone numbers will be fed directly into the MOTECH database for provision of program services. For pregnant women, additional data collected as part of baseline household surveys include demographic factors (age, education, parity, literacy), socioeconomic characteristics (household assets, conditions), health care seeking and practices, as well as data on digital literacy and phone access. These data can be linked to MOTECH, IVR, and call center records to provide additional data elements. Overall, these data as well as data on technology performance (receipt of messages) and user engagement (behavioral performance) with content will help estimate exposure to Kilkari used in the assessment of causality as part of the RCT. For ASHAs, baseline survey data will include similar data elements on demographic, socioeconomic, and mobile literacy and phone access as well as knowledge and work-related variables linked to reported motivation and satisfaction. Overall, these added data elements can be linked to IVR and call record data for this subpopulation of Mobile Academy and Kilkari users in four districts of MP where the RCT is underway.

### Data Processing and Analysis

Descriptive statistics, including univariate plots like histograms, will be used to understand the distribution of each variable, including skewness and outliers. Multivariate plots like scatterplots and

locally weighted scatterplot smoothing (LOWESS) lines will be used to understand the relationships between different variables. Efforts to prepare the data are divided into two parts: splitting data into training and testing groups, and data processing.

#### Splitting Into Training and Testing

To avoid overfitting models that work well for the data in hand but fail to predict well with other datasets, the data will be split into three components. This is possible due to the large size of the dataset. The training set will comprise 60%, the test dataset 20%, and the validation dataset 20% of the data. The test set will be used to test and fine-tune the accuracy of predictive models, and the final selected model will be applied to the validation dataset. We anticipate having data from 2017, 2018, and 2019 and will ensure equal representation by random sampling. To ensure that the data are controlled for time as a confounder, subsets will be equally represented across different time periods.

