**Methods:**

Study participants include pregnant and postpartum women (Kilkari) as well as frontline health workers (Mobile Academy) across 13 states in India. Data elements are drawn from system-generated databases used in the routine implementation of programs to provide users with health information. We explain the structure and elements of the extracted data and the proposed process for their linkage. We then outline the various steps to be undertaken to evaluate and select final algorithms for identifying gaps in data quality, poor user performance, predictors for call receipt, user listening levels, and linkages between early listening and continued engagement.

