Study aims.Aim 1: Describe subscriber losses at different points during pregnancy and postpartum period from the programObjective 1a. Determine differences in subscribers who remain subscribed to Kilkari throughout the duration of service versus those lost at different points along the continuum of program databases.Objective 1b. Develop a classifier for identifying different categories of losses.Aim 2: Facilitate the program’s ability to identify and target ASHAs likely to perform poorly on digital health training programs and knowledge assessmentsObjective 2a. Determine predictors of training course completion (overall and time to completion) by ASHAs based on performance on early modules of the course and other characteristics including reported motivation, knowledge, individual characteristics, and mobile literacy.Objective 2b. Develop a classifier for the routine identification of ASHAs likely to perform poorly.Aim 3: Understand the factors underpinning successful receipt of calls (are calls received?)Objective 3a. Determine what proportion of calls successfully reach the end-user’s device for Kilkari.Objective 3b. Identify the proportion of content specific to infant feeding and family planning received by end-users for Kilkari.Aim 4. Determine how users are listening to messagesObjective 4a. Determine predictors for exposure to Kilkari content based on user characteristics.Objective 4b. Measure exposure to Kilkari content based on technological and behavioral (end-user engagement) performance.Objective 4c. Develop a classifier for measuring listening levels.Aim 5: Understand optimal message delivery options for maximal impactObjective 5a. Determine message delivery options with the most success in engaging client and assess patterns of listening.Objective 5b. Determine the effect of early listening patterns (time of day of listening, duration and frequency of listening, content listening patterns) on postpartum engagement and overall exposure.

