**Supervised**				
	1 Logistic regression	Classification (nonlinear model)	Classification of ASHA workers by user characteristics and patterns of training initiation by ASHAs	User characteristics associated with exposure to messaging content and duration in MP where face-to-face survey data have been collected
	2 Linear discriminant analysis	Classification (linear model). It is a linearization of Gaussian naïve Bayes.	Classification of ASHA workers by user characteristics and patterns of training initiation, completion, and performance	User characteristics associated with exposure to messaging content and duration
	3 Support vector machines (SVMs)	SVMs are techniques based on the calculation of the maximum margin hyperplane for the classification problems	Classification of ASHA workers by user characteristics and patterns of training initiation and completion	User characteristics associated with exposure to messaging content and duration
	4 Classification and regression trees	Predictive model that consists of leaves that represent the target and branches that represent conjunctions of inputs features. Considered a subset of decision trees. Random forests operate by constructing multiple decision trees during training and aggregating their results to avoid overfitting by single trees.	Classification of ASHA workers by user characteristics and patterns of training initiation and completion	User characteristics associated with exposure to messaging content and duration
	5 Naïve Bayes	Classification model based on probabilities	Classification of ASHA workers by user characteristics and patterns of training initiation and completion	User characteristics associated with exposure to messaging content and duration
	6 Neural Networks (NNs)	NNs are powerful models for machine learning. They are a generalization of linear and nonlinear models	Classification of ASHA workers by user characteristics and patterns of training initiation and completion	User characteristics associated with exposure to messaging content and duration

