### Testing and Validation

To facilitate decision making on the optimal analytic approach, three steps will be undertaken: (1) develop the correct model for each algorithm using the training dataset, (2) apply the final model for each algorithm on the test dataset, and (3) apply the best performing algorithm on the validation dataset.

In Step 1, algorithms will be run using the training dataset comprising 60% of the total sample from across all states for which data are available. For each algorithm, iterative testing will be run to select the best model that fits the data. The emerging results will then be assessed for model fit and accuracy. Table 4 summarizes the four proposed metrics for assessing the performance of each model.

**Table 3 table3:** Performance comparisons of learning algorithms modified from Kotisiantis et al [17,18] (++++ represents the best and + the worst performance).

Model attributes	Decision trees	NNs	Naïve Bayes	SVM	Linear discriminant analysis	Logistic regression
Accuracy in general	++	+++	+	++++	+++	++
Speed of learning with respect to number of attributes and number of instances	+++	+	+++	+		
Speed of classification	++++	++++	++++	++++	++++	++
Tolerance to missing values	+++	+	++++	++	+++	+
Tolerance to irrelevant attribute	+++	+	++	++++	+++	+
Tolerance to redundant attributes	++	++	+	+++	++	+
Tolerance to highly interdependent attributes	++	+++	+	+++	++	+
Dealing with discrete/ binary/ continuous attributes	++++	+++ (not discrete)	+++ (not continuous)	+++ (not discrete)	++++	+++
Tolerance to noise	++	++	+++	++	+++	++
Dealing with danger of overfitting	++	+	+++	++	++	+
Attempts for incremental learning	++	+++	++++	++		
Explanation ability/ transparency of knowledge/ classification	++++	+	++++	+	+	+
Model parameter handing	+++	+	++++	+	++	+

**Table 4 table4:** Metrics for assessing the performance of each model.

Model metrics	Formula^a^	Description
Accuracy	(TP+TN)/(TP+TN+FN)	Proportion of cases correctly classified
Precision or positive predictive value	TP/(TP+FP)	Fraction of relevant instances among the retrieved instances
Sensitivity or recall	TP/(TP+FN)	Fraction of relevant instances retrieved over total amount of relevant instances

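### The dataset-size argument for the 60/20/20 split is not shown to hold for models that need the four-district MP survey variables, whose linked sample size is not stated

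*Protocol article*

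**What the plan says.** The section on splitting into training and testing sets one rule: "The training set will comprise 60%, the test dataset 20%, and the validation dataset 20% of the data". Its reason is "This is possible due to the large size of the dataset". On the second component it says: "The test set will be used to test and fine-tune the accuracy of predictive models". The selected model then goes to the validation component. Testing and Validation repeats this as a three-step path and defines the first step on the national data: "algorithms will be run using the training dataset comprising 60% of the total sample from across all states for which data are available". The article describes no cross-validation, bootstrap or other resampling scheme.

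The abstract places participants, including "frontline health workers (Mobile Academy) across 13 states in India", in the main data. The section on additional baseline-survey data says that survey variables can be linked only "for this subpopulation of Mobile Academy and Kilkari users in four districts of MP where the RCT is underway". Two planned analyses draw on them:

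- **Kilkari.** In Table 2 the logistic regression row is limited to users "in MP where face-to-face survey data have been collected". The other supervised rows carry no such limit.
- **Mobile Academy.** Objective 2a in the study aims textbox predicts course completion from early-module performance and "other characteristics including reported motivation, knowledge, individual characteristics, and mobile literacy". The baseline-survey section gives the ASHA survey as the source of motivation, knowledge and mobile literacy.

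The Discussion (Principal Considerations) gives the same ASHA survey variables a different role. There, predictors built on early-module performance are to be externally validated with them.

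**The concern.** The plan makes a large dataset the condition for a three-way split, then includes analyses that can use only a small geographic part of that dataset. The number of surveyed women and ASHAs appears nowhere, so a reader cannot tell whether the condition is met for them.

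If the linked sample is modest, two things suffer. The model is fitted on fewer people than were surveyed, and both its selection and its reported performance depend on which people one random draw placed in the two 20% parts. The article intends the predictors to show which women a program misses and which ASHAs are less likely to finish, so an unlucky split could carry through into targeting.

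**Working it through.** **Step 1. No figure to reproduce.** The article gives fractions only, and they sum correctly (60 + 20 + 20 = 100). It states no total N and no survey N. Every N below is an assumption.

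**Step 2. What the split does to the surveyed people.** Let N be the number of surveyed people linked to system data. If the split is made within the subset, the parts are 0.60N, 0.20N and 0.20N. If it is made at random on the all-state total, a random 20% of the total contains 20% of the subset in expectation, so the expected parts are the same. Either way, 0.20N + 0.20N = 0.40N is withheld from fitting.

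**Step 3. Precision of one model's accuracy on the test set.** SE = sqrt(p(1 − p)/n), with n = 0.20N and p = 0.75 assumed, so p(1 − p) = 0.1875.

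| Linked N (assumed) | Fitted, 0.60N | Test, 0.20N | SE of 75% accuracy |
|---|---|---|---|
| 300 | 180 | 60 | sqrt(0.1875/60) = 5.6 points |
| 1,500 | 900 | 300 | sqrt(0.1875/300) = 2.5 points |
| 5,000 | 3,000 | 1,000 | sqrt(0.1875/1,000) = 1.4 points |
| 10,000 | 6,000 | 2,000 | sqrt(0.1875/2,000) = 1.0 point |

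**Step 4. Choosing between models.** Step 3 concerns one model. Candidates scored on the same records have correlated errors, so selection needs a paired calculation. Assume six classifiers, one with true accuracy 80% and five with 78%, and a latent correlation of 0.8 between their errors. The simulated chance that the truly best one scores highest on the test set, ties shared, is:

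| Linked N (assumed) | Test n | Chance of choosing the best |
|---|---|---|
| 300 | 60 | 31% |
| 1,000 | 200 | 46% |
| 2,000 | 400 | 62% |
| 5,000 | 1,000 | 82% |
| 10,000 | 2,000 | 96% |

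This applies only where several algorithms compete on the subset. Table 2 lists six supervised algorithms for the ASHA task. For Kilkari it ties only logistic regression to the MP survey.

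**Step 5. Single split against 10-fold cross-validation.** In a simulation with assumed effects (200 runs), the standard deviation of estimated accuracy was:

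| n | Single split | 10-fold cross-validation |
|---|---|---|
| 300 | 6.5 points | 2.7 points |
| 1,200 | 2.8 points | 1.4 points |
| 5,000 | 1.4 points | 0.6 points |

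The direction is the same at each size tried. The absolute gain shrinks from 6.5 − 2.7 = 3.8 points to 1.4 − 0.6 = 0.8 points. The exact sizes depend on the assumed effects.

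**The case against.** The strongest reply has four parts.

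1. **No survey size is given.** A reader might infer that the split produces small test sets and unstable model choice. The documents do not support that as a fact: with an assumed 5,000 to 10,000 linked people the test set has 1,000 to 2,000 records, and the paired calculation picks the best model 82% to 96% of the time. This part stands, and the point has to be conditional on N.
2. **The split is defined on the all-state total, and an article may leave a sub-analysis to a fuller plan.** The article does not expressly apply 60/20/20 within the MP subset. But it states one path and one condition for that path, and a random national split still leaves only about 20% of surveyed people in each of the two smaller parts. The point concerns a stated justification that does not reach certain stated analyses, so it is more than an omitted detail. The chance that a fuller plan deals with it limits the severity.
3. **The affected analyses are narrower than they look.** Objective 2a also uses early-module scores, age and location, which are program data not confined to MP. The Discussion casts the survey variables as external-validation data, and no contest between algorithms is stated for Kilkari within MP. All of this stands. What remains is the survey-variable part of Objective 2a, where the predictor role is explicit, and the Kilkari logistic regression, where Testing and Validation still calls for iterative model selection within each algorithm.
4. **The standard error of one accuracy is not that of a difference.** This is correct. Step 3 measures the precision of reported performance and does not show that differences between models lie within chance.

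**Conclusion.** The concern holds in a limited form. Dataset size is the only reason given for the single split, and it is not shown to apply to the Kilkari logistic regression or to the motivation, knowledge and mobile-literacy predictors of Objective 2a. Following the stated path would withhold about 40% of surveyed people from fitting.

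The consequence ranges from material to minor. At 300 to 1,500 linked people the reported accuracy carries a standard error of 5.6 to 2.5 points from the test set alone. At 5,000 or more the loss is small. These figures rest on assumed values of N, true accuracy and, in Steps 4 and 5, model differences or effects. The split of the national system data is not in question. Separately, the study aims and the Discussion disagree on whether the ASHA survey variables are predictors or external-validation data, and the answer decides whether the Mobile Academy half of this point applies.

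**What to change.** Keep 60/20/20 for the national system data and for the part of Objective 2a that uses only program data. Then make four changes:

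- For any model that uses MP survey variables, replace the single split with 10-fold cross-validation, preferably repeated, with tuning nested inside and folds kept whole by woman or ASHA. Bootstrap optimism correction is an alternative.
- State the number of surveyed women and of surveyed ASHAs linked to system data.
- Report intervals for paired performance differences between candidate models.
- Reconcile Objective 2a with the Discussion on the role of the ASHA survey variables.

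Possible wording: *Models that include MP baseline-survey variables will be tuned and assessed by repeated 10-fold cross-validation with nested tuning, all records of a woman or ASHA staying in the same fold; the linked sample size and intervals for paired performance differences will be reported.*

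The cost is a few sentences and more computing time, with no new data. The real downside is that this subset would no longer have an untouched hold-out set.

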## Introduction

Machine learning is an application of artificial intelligence that aims to allow computers to learn automatically from the analysis of large, highly granular datasets, with minimal human intervention [1]. In machine learning, models are created using existing data to make predictions about future events. Applications of machine learning in global public health are emerging, particularly in the context of digital health solutions, which have the potential to generate “big data.” Digital health encompasses the subsectors of health information technology, mobile health (mHealth), electronic health (eHealth), telehealth, and telemedicine.

Machine learning approaches in digital health have been mainly in the area of analyzing data generated by wearable sensors and accelerometers including efforts to predict and personalize monitoring systems for mobile patients [2], predict physical activity type and energy expenditure [3-5], and falls [6]. Beyond analyses of accelerometer data, studies have explored user engagement with different apps on mobile phones and tablets [7], and responses to patient feedback on health services [8]. Similar applications to social media data have sought to improve the detection of online illegal drug sales [9], depression [10,11], as well as explore vaccination sentiment trends and improve disease identification [12]. Analyses of geographic information system data have been used to map risk of exposure to disease [13]. Collectively these varied applications of machine learning have been classified by Mooney et al in three broad categories of (1) surveillance, including systems to monitor trends in disease incidence, health behaviors, and environmental conditions, (2) hypothesis-generating research, and (3) causal inference [1].

Evidence gathering on the effectiveness of digital health solutions is a growing field [14]. However, very few evaluations have sought to incorporate machine learning algorithms [8], and broader guidelines on the monitoring and evaluation of digital health solutions have stopped short of outlining options for predictive modeling [15]. Appropriate implementation of machine learning methodologies can facilitate dynamic, real-time interventions to improve data collection to assess program effectiveness and can also inform how data are used prospectively to improve program implementation.

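### Giving the training, test and validation subsets the same mix of time periods does not control confounding by time, and leaves performance in a later period untested

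*Protocol article*

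**What the plan says.** The section Splitting Into Training and Testing gives the proportions: "The training set will comprise 60%, the test dataset 20%, and the validation dataset 20% of the data". The split is meant to avoid models that suit the data in hand but "fail to predict well with other datasets". On calendar time it says: "We anticipate having data from 2017, 2018, and 2019 and will ensure equal representation by random sampling", and then: "To ensure that the data are controlled for time as a confounder, subsets will be equally represented across different time periods".

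The article names no calendar-period term in any model, no hold-out of a later period and no unit of split (person, subscription or call record).

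Four other places bear on the point:

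- **Study aims (textbox).** Objectives 2a and 4a report predictors of course completion and of exposure to Kilkari content. Objective 2b reads: "Develop a classifier for the routine identification of ASHAs likely to perform poorly".
- **Analysis.** MOTECH was integrated with RCH in mid-2017. Multiple subscriptions on one mobile number ended on July 28 (RCH) and October 6 (MCTS) of that year. The section gives the likely horizon as 2017-2018, whereas the splitting section expects data from 2019 as well.
- **Analysis, on identifiers.** "MCTS tracks pregnancies and births, rather than women", while RCH holds a beneficiary ID for each woman.
- **Discussion, Principal Considerations.** The external validation planned for Mobile Academy uses further ASHA characteristics, not a later period.

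**The concern.** Confounding by time arises when both a predictor and the outcome change over calendar time. It is dealt with by conditioning on time, through a model term, stratification or reporting within period. Matching the period mix of three subsets does none of these. It fixes how the subsets compare with each other and leaves the relation between period, predictor and outcome within each one untouched.

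Two things are at stake. First, a false predictor found in training will reappear in test and validation, because each subset carries the same confounding, so the validation step would seem to confirm it. Second, no subset is later than the training data, so nothing in the plan shows how a routinely used classifier performs on the next intake of ASHAs or subscribers.

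**Working it through.** **The plan's own figure.** 0.60 + 0.20 + 0.20 = 1.00, so the split is complete. The article gives no year effects or drift. All values below are assumptions chosen to show the mechanism, not estimates for this study.

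**Step 1. Does an equal period mix control time?** Take three equally represented years. Let a binary predictor X have prevalence 0.20, 0.50 and 0.80 by year, and the outcome Y have risk 0.20, 0.35 and 0.50. Within each year X and Y are independent, so the true within-year odds ratio is 1.00. Pooled over years:

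- P(X=1) = (0.20 + 0.50 + 0.80)/3 = 0.50
- P(Y=1) = (0.20 + 0.35 + 0.50)/3 = 0.35
- P(X=1, Y=1) = (0.20×0.20 + 0.50×0.35 + 0.80×0.50)/3 = 0.615/3 = 0.205
- P(Y=1 | X=1) = 0.205/0.50 = 0.41
- P(Y=1 | X=0) = (0.35 − 0.205)/0.50 = 0.29
- Crude odds ratio = (0.41/0.59)/(0.29/0.71) = 1.70

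This depends only on the year mix. Subsets with the same year mix therefore share the same false odds ratio. A simulation of 300,000 records with a year-stratified 60/20/20 split (year shares 33.4/33.3/33.3% in every subset) agrees:

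| Subset | Crude odds ratio | Odds ratio adjusted for year |
|---|---|---|
| Training | 1.71 | 1.01 |
| Test | 1.65 | 0.96 |
| Validation | 1.73 | 1.00 |

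Balance removes none of the confounding. A year term removes it.

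**Step 2. Can the validation set show later performance?** The outcome follows a logistic model with one continuous predictor. The intercept is −0.5, −0.2 and 0.1 by year, and the slope varies by scenario. The random split fits on the 60% and validates on the 20%. The out-of-time test fits on years 1-2 and tests on year 3.

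| Slopes in years 1, 2, 3 | AUROC, random split | AUROC, out of time | Mean predicted − observed, random split | Mean predicted − observed, out of time |
|---|---|---|---|---|
| 1, 1, 1 | 0.737 | 0.740 | −0.001 | −0.093 |
| 1, 0.7, 0.4 | 0.673 | 0.607 | −0.002 | −0.097 |
| 1, 0.5, 0 | 0.626 | 0.500 | −0.001 | −0.100 |

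The AUROC difference (random minus out of time) is −0.003, 0.066 and 0.126. With a stable slope, discrimination carries over fully. When the outcome level moves by year, predicted risk is about 0.09 to 0.10 too low in the later year even in that case. The random-split validation shows good calibration in all three scenarios and so cannot tell them apart.

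**Step 3. Which period could be held out?** Service runs from the second trimester to the child's first birthday, about 6 + 12 = 18 months for a woman enrolled at the start of that trimester. For full-course Kilkari outcomes, data to the end of 2018 complete follow-up only for such women activated by about mid-2017. Data to August 2019, the month in which results are due, would extend this to about February 2018. The difference between the two stated horizons therefore decides whether a usable later cohort exists for those outcomes.

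**The case against.** The strongest reply is that the stated aim of the split is to guard against overfitting, which a random hold-out does. Temporal validation is a stronger design, and its absence is not in itself an error. That stands, and it is why the second part of this point is a limitation and not a mistake. It does not rescue the claim about confounding, which is made outright and is incorrect.

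It can also be said that the analysis window was chosen to follow the 2017 system changes. If the data begin after October 6, 2017, those changes would not act within them. The article says only that the horizon may lie in 2017-2018 after the changes, and the splitting section expects 2017 data without a start month. The changes are one possible source of period effects, not a demonstrated one.

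Three stronger readings are tempting, and the article does not support them:

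- **That validation performance is overstated and will not hold.** Step 2 shows no loss of discrimination without drift in the predictor effect, and the article gives no drift.
- **That future prediction is the stated purpose of every model.** The Introduction's sentence, "In machine learning, models are created using existing data to make predictions about future events", is a general definition for lay readers. Several objectives (1a, 3a, 3b, 4b) describe or measure. Objective 2b, and the Discussion's mention of prediction tools for implementers, are the better basis.
- **That one woman's records will fall in all three subsets.** The unit of split is not named. The performance metrics count ASHAs, that is, persons, and the beneficiary ID reached MOTECH and Kilkari in December 2016, before the analysis window. If MCTS gives two records per pregnancy (mother and child), a record-level split would part them with probability 1 − (0.6² + 0.2² + 0.2²) = 0.56, but two records cannot occupy three sets. Larger overlap needs many records per woman, and inflated performance also needs a model that learns the individual. The article states neither. This is an open risk that an article may leave to a fuller plan.

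**Conclusion.** The sentence claiming control of time is wrong as written and should be removed. This follows from the definition of confounding and needs no assumption. The size of any resulting bias does need one: the odds ratio of about 1.7 for a null predictor rests on assumed shifts of 0.20 to 0.80 in the predictor and 0.20 to 0.50 in the outcome over three years.

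The plan also cannot show how its classifiers perform in a later period. This matters for Objective 2b and less for the descriptive aims. The cost could be nil or substantial (AUROC difference from about 0 to 0.13 in the assumed scenarios), and the present design would not reveal which. Overlap of persons between subsets is not an established fault.

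**What to change.** 1. Delete the statement that balanced subsets control time. Equal representation may stay, described as making the subsets comparable.
2. In the models that report predictors (Objectives 2a and 4a), include calendar period and source system (RCH or MCTS) as terms, or report results within period.
3. Add an out-of-time check for classifiers meant for routine use: train on earlier activations and test on the latest cohort with complete follow-up for the outcome in question. Use a model without period indicators here, since the indicator for a held-out period cannot be estimated.
4. Reconcile the 2017-2018 horizon in Analysis with the 2017-2019 data in Splitting Into Training and Testing, and state the start month, before choosing the held-out period.
5. As a safeguard, assign each RCH beneficiary ID and each ASHA ID wholly to one subset. Where no beneficiary ID exists, use a de-identified phone-number key. Women sharing a phone would then stay together, which is harmless for this purpose, but the key must be made when the files are merged and de-identified.

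The cost is a few sentences, some extra analysis and possibly lower reported performance. For full-course Kilkari outcomes the held-out cohort may be small or absent, in which case the check should use outcomes with shorter follow-up and the limitation should be stated.
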